### Study Design

As you can see in Figure 2 the ci-chimps study is a two-group randomized controlled multicenter trial with assessments at baseline as well as at 12- and 24-months follow-up. It is one part of the superior project CHIMPS-NET, wherefore an own study protocol is in preparation (9). The ci-chimps study will be conducted from January 2020 to September 2023. The ci-chimps project's preparation phase includes the translation of the questionnaires FFMHPQ and the ICQ and the randomization of the clinical centers. The first measurement (baseline) takes place from January 2020 to May 2021. We stopped the baseline assessment after the last implementation intervention and defined this point as the end of the implementation interventions. During this year we implemented the superior project CHIMPS and the three implementation interventions of ci-chimps in the clinical centers. The second assessment will be in May 2022 and the follow-up in May 2023.

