### Study Setting

At the beginning of the study, 21 clinical centers located in 15 federal states in Germany were part of the CHIMPS-NETwork. Each clinical center has two subordinate clinics: one of the children and adolescent psychiatric department and one of the adult psychiatric department. Only 19 of the 21 clinical centers were randomized such that nine centers will receive additional support of all of the three implementation interventions (intervention group), and the remaining 10 clinical centers will be the control group and will not get specific implementation support. Hamburg (University Medical Centre Hamburg-Eppendorf, Germany), as the headquarter, and Munich (University Medical Center, Department of Psychiatry and Psychotherapy, Munich, Germany) are conducting their own study) are not randomized. Unfortunately, one clinical center of the intervention group left the study after a few weeks, so eight clinical centers remain in the intervention group and 10 in the control group. Because we defined the number of cases per clinical center, the unequal allocation to the intervention and control group leads to the consequence that the number of cases is different for the intervention- and the control group (TAU) as seen in Figure 1.

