#### Criteria for Inclusion

Every employee involved in the treatment of the patients (Medicine, Psychology, Nurses) of every clinical center that is part of the CHIMPS-NET project will be invited to participate in the ci-chimps study.

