### Outcome Measures

#### Sociodemographic Questions

Besides age, gender and profession, we record with a specifically designed questionnaire, in which clinical center the employees work, how long they have been employed there and how strongly they are involved in the CHIMPS-NET-project.

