### Statistical Analysis

#### Data Coding and Analysis

All statistical analyses will be performed with SPSS (version 26.0 or newer). Means and standard deviations or median and 1st and 3rd quartiles, as appropriate, for the continuous variables as well as absolute and relative frequencies for the categorical variables of the whole sample and the respective treatment groups will be calculated and presented. The primary analysis will be conducted with the intention to treat (ITT) population consisting of all employees. The employees of a clinical center are subject to the same influences and cluster effects. Hence, for the primary endpoint, operationalized as the difference to baseline, a mixed linear model will be performed with treatment group, time, and baseline value as fixed effects, and clinical center as a random effect. The interaction between the treatment group and time will be tested and will be eliminated from the model if it is not statistically significant. The result of the primary analysis is the contrast of the treatment group after 18 months. Only this result will be considered in a confirmatory manner. The two-sided type I error will be set to 5%. It is possible that the fluctuation of employees in the clinical centers is so low that we can extend the model to a longitudinal model. The secondary endpoints will be examined in an exploratory manner with the same model in the case of continuous endpoints and with a similarly mixed Poisson regression in the case of count data. Results will be reported and published according to the CONSORT statement for cluster randomized trials (34).

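### The primary model leaves out profession, which the trial already records; prespecifying it is a nearly free, modest improvement rather than the repair of an error

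*Protocol article*

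**What the plan says.** Data Coding and Analysis sets out the confirmatory analysis. The outcome is change, "for the primary endpoint, operationalized as the difference to baseline", and "a mixed linear model will be performed with treatment group, time, and baseline value as fixed effects, and clinical center as a random effect". A group-by-time interaction is tested and dropped if it is not significant. No other covariate is named, and only the treatment contrast from this model is confirmatory.

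The staff who answer are mixed by design. Under Criteria for Inclusion, those invited are "Every employee involved in the treatment of the patients (Medicine, Psychology, Nurses) of every clinical center". Under Study Setting, "Each clinical center has two subordinate clinics: one of the children and adolescent psychiatric department and one of the adult psychiatric department". Under Sociodemographic Questions the article says: "Besides age, gender and profession, we record with a specifically designed questionnaire, in which clinical center the employees work". Length of employment and degree of involvement in the project are recorded as well. Department is not in that list.

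On timing, Study Design puts "the randomization of the clinical centers" in the preparation phase. Baseline assessment ran from January 2020 to May 2021 and closed after the last implementation intervention. The Discussion concedes that the same employees cannot be guaranteed at every measurement. Data Coding and Analysis treats a longitudinal model as a possible extension, to be used only if staff turnover is low.

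**The concern.** Physicians, psychologists and nurses plausibly differ in how they answer a questionnaire on family-oriented practice. The Background lists job role, training and skills among the practitioner factors behind such practice. A covariate that predicts the outcome and is already in the data set would normally be a candidate for the primary model.

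The way staff enter the trial adds to the case. Randomization balances centers in expectation. It does not balance who replies to an invitation once a center's allocation is settled, particularly when baseline stayed open while the implementation interventions were delivered. If respondents also change between waves, the mix can shift over time within a center.

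Two things are at stake: some precision in a trial with only 18 centers, and some protection of the confirmatory contrast against observed differences in respondent mix. The second can reach the primary result only if the covariate is fixed in advance. Added after the data are seen, it would be a post hoc choice.

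**Working it through.** **Inputs from the article.** Difference 0.4 SD, two-sided 5%, 80% power, ICC 0.05, 18 centers with 31 employees each, 30% incomplete questionnaires (Sample Size and Power Calculation); final allocation 8:10 centers (Randomization).

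**Input assumed.** The share of variance that the added covariates explain. The article gives none, so a range is shown.

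**Step 1: reproduce the plan's figure.** With total variance 1, a center mean has variance 0.05 + 0.95/31 = 0.0806. SE = √[0.0806 × (1/k₁ + 1/k₂)], and power comes from the noncentral t distribution with 18 − 2 = 16 df and noncentrality 0.4/SE.
- 9 against 9 centers: SE = √(0.0806 × 0.2222) = 0.134; power 80.1%. With 30 per center it is 79.6%, so 31 is the smallest sufficient size, and 31 × 18 = 558.
- 558/0.70 = 797.1, rounded up to 798.

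Both stated figures are reproduced with no covariate gain at all.

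**Step 2: the allocation as it stands.** 8 against 10 centers: SE = √(0.0806 × 0.225) = 0.135; power 79.6%.

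**Step 3: what adjustment could add.** If the covariates explain a fraction R² of the within-center variance only, the center-mean variance becomes 0.05 + 0.95 × (1 − R²)/31.

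| R² within center (assumed) | SE | Power |
|---|---|---|
| 0 | 0.135 | 79.6% |
| 5% | 0.133 | 80.4% |
| 10% | 0.132 | 81.1% |
| 20% | 0.130 | 82.6% |
| 30% | 0.127 | 84.2% |

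The gain is limited because 0.05/0.0806 = 62% of the center-mean variance lies between centers, where a purely within-center covariate does nothing. If the covariates also explained 20% of the between-center variance, power would be 85.3% to 89.1% for R² of 5% to 30%. Nothing in the article supports counting on that.

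**Step 4: when bias could arise.** To a first approximation, bias = (difference between arms in the share of a staff group) × (difference between staff groups in change, given baseline). It is zero if either factor is zero. The article gives no value for either.

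**Step 5: what the baseline terms cover.** The article does not say whether the baseline value is the employee's own.
- If it is, stable differences between professions are largely absorbed, and an employee without a baseline has no change score and cannot enter this model. What remains is a difference in change given baseline among linked staff.
- If a center-level baseline stands in because respondents change, a shift in staff mix between waves is not absorbed.

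**Step 6: what is available.** Profession is recorded. Department is not listed, and center cannot stand in for it, because every center contains both departments.

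**The case against.** The strongest case against is that nothing here is wrong. The model is valid without profession, the sample size counts on no covariate, and further covariates and sensitivity analyses often appear in an analysis plan, which is not shown. The article also plans frequencies of categorical variables by treatment group, so profession by arm would probably be tabulated anyway. Most of this stands, and it is why the point is an improvement and not an error. It does not dispose of the point, because the article does not leave the covariates of its confirmatory model open: it lists them.

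A reader might go further and infer a sizeable bias. For example, a 0.5 SD gap between departments and a 20-point difference in department share between arms would give 0.5 × 0.20 = 0.10 SD, or 25% of the planned 0.4. The documents do not support this, for three reasons.
- Neither figure comes from the article, and the 0.5 SD is a gap in level. The planned model analyses change and adjusts for baseline, so only a gap in change given baseline counts.
- Chance differences in mix between centers are already carried into the standard error by the random center effect. Counting them again as bias is double counting. Only selective response by arm is bias, and adjusting for profession would not remove selection of motivated staff within a profession.
- Department is not listed as recorded, so it cannot be assumed to be at hand.

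Nor should one infer that planned precision has been lost, since none was planned from this source.

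**Conclusion.** The point holds as a recommendation. The primary model omits a covariate that is already collected and plausibly prognostic, in a trial whose participants join around and after allocation and may change between waves. On power alone the gain is about 1 to 5 percentage points (79.6% to 80.4-84.2%), assuming that the covariates explain 5-30% of the within-center variance and none of the between-center variance. Protection against a differing respondent mix is a real but unquantified benefit. It matters only if response is selective by arm and profession or department predicts change given baseline. No bias figure should be attached to it.

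**What to change.** Add profession (medicine, psychology, nursing) as a prespecified fixed effect in the primary model. Add department (child and adolescent against adult psychiatry) only if it was captured at employee level; the article does not list it. Report the model without these terms as a sensitivity analysis, and tabulate respondents by profession, arm and wave.

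The cost is two employee-level degrees of freedom for profession and one more for department if it is available. The 16 center-level degrees of freedom that govern the treatment contrast are untouched. No new data are needed for profession. The change should be written down before outcome data are examined.

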### Participants

#### Sample Size and Power Calculation

This study will be conducted in 18 clinical centers and 31 employees on average per clinical center will be required to detect a difference at 12 and 24 months follow-up regarding family-oriented practice measured with FFMHPQ between the clinical centers receiving the support of the three implementation interventions and the clinical centers not receiving the support of the implementation interventions of 0.4 (Cohen's d) with 80% power, a two-sided alpha of 5% and a cluster effect of 5% (intraclass correlation coefficient of 0.05). This results in a sample size of 558 employees (31 per clinical center). Assuming a proportion of 30% incompletely completed questionnaires, we aim to recruit 798 employees.

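### A significance pre-test on group-by-time decides which effect the only confirmatory contrast measures, and that contrast is named at 18 months, where nothing is assessed

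*Protocol article*

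**What the plan says.** Protocol article, Data Coding and Analysis: the primary endpoint is change from baseline, for which "a mixed linear model will be performed with treatment group, time, and baseline value as fixed effects, and clinical center as a random effect". On the group-by-time term: "The interaction between the treatment group and time will be tested and will be eliminated from the model if it is not statistically significant". Then: "The result of the primary analysis is the contrast of the treatment group after 18 months", followed by "Only this result will be considered in a confirmatory manner". The type I error is 5% two-sided.

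Protocol article, Study Design: a "two-group randomized controlled multicenter trial with assessments at baseline as well as at 12- and 24-months follow-up". The section Sample Size and Power Calculation refers to a difference at 12 and 24 months, and hypothesis H1 also names both follow-ups.

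The article does not say how time is coded, at what level the interaction is tested, or what the contrast means once the interaction is gone.

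**The concern.** With the interaction in the model, the group contrast belongs to one time. Without it, there is a single group coefficient pooled over both follow-ups. The trial data choose between the two through a significance test, and the reported interval is computed as if the choice had been fixed. The sample size covers the group difference only, not this pre-test.

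A second defect determines how much this matters: the named time, 18 months, is not an assessment time. If the intended target is 24 months, a fading effect would often go undetected by the pre-test, and an average containing the stronger 12-month effect would be reported as the late effect. The one confirmatory result would then have no fixed meaning.

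**Working it through.** **The plan's own figure.** From Sample Size and Power Calculation: 18 centers, 31 employees per center, d = 0.4, ICC 0.05, 80% power, two-sided 5%. With 9:9 centers:
- Variance of a center mean = (1 + 30 × 0.05)/31 = 0.08065.
- SE of the difference = √(2/9 × 0.08065) = 0.1339, and 0.4/0.1339 = 2.99.
- A noncentral t with 16 df gives 80.1% power (79.6% with 30 per center). So 31 is the minimum and 18 × 31 = 558 is reproduced; 558/0.7 = 797.1, rounded up to 798.
- With the actual 8:10 allocation, power is 79.6%.

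**Reading A: time linear, contrast at 18 months.** The full-model contrast is the mean of the 12- and 24-month contrasts. With equal numbers the reduced model targets the same value: effects 0.4 and 0 give 0.20 in both. With an assumed 31 and 22 respondents per center, the reduced model gives 0.4 × 31/53 = 0.234 against 0.20.

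**Reading B: time as a factor.** An 18-month contrast cannot be estimated. The plan has to be read as meaning an assessed time; 24 months is taken here.

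Assumptions for reading B: SD 1, 8:10 centers, 31 per wave, pre-test at two-sided 5%, normal approximation. Neither within-employee correlation r nor center autocorrelation c is given in the article, so r is 0 or 0.5 and c is 1 or 0.8.
- Variance at one time: V = (1/8 + 1/10) × (0.05 + 0.95/31) = 0.01815; SE 0.135.
- Covariance between times: C = 0.225 × (0.05c + 0.95r/31). For r = 0, c = 1, C = 0.01125.
- Interaction SE = √(2(V − C)) = √0.0138 = 0.117.
- SE of the average = √((V + C)/2) = √0.0147 = 0.121.
- Pre-test power for a 0.2 SD difference: Φ(0.2/0.1174 − 1.96) = Φ(−0.26) = 40%. For 80% power the difference must be about 2.80 × 0.1174 = 0.33 SD.

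The interaction and the average are uncorrelated when both times have equal variance. So with effects 0.4 and 0.2, the contrast after removal averages (0.4 + 0.2)/2 = 0.30. That scenario is the 0.2-then-0 scenario shifted by 0.2, so coverage of the 24-month effect is 100% minus the rejection rate for 0.2 then 0. Rejection rates come from 1,000,000 normal draws per scenario.

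| r | c | SE interaction | SE average | Pre-test power at 0.2 | Dropped (0.4 then 0.2) | Rejects (0.2 then 0) | Coverage (0.4 then 0.2) | Rejects (0 and 0) | Rejects (0.4 and 0.4) |
|---|---|---|---|---|---|---|---|---|---|
| 0 | 1 | 0.117 | 0.121 | 40% | 60% | 10.0% | 90.0% | 5.5% | 90.1% |
| 0 | 0.8 | 0.135 | 0.117 | 32% | 68% | 11.4% | 88.6% | 5.7% | 91.9% |
| 0.5 | 1 | 0.083 | 0.128 | 67% | 33% | 7.2% | 92.8% | 5.3% | 87.3% |
| 0.5 | 0.8 | 0.107 | 0.124 | 47% | 53% | 9.2% | 90.8% | 5.4% | 89.1% |

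A fixed 24-month contrast rejects in 5.0% when the 24-month effect is 0, and in 84% when it is 0.4. If the effect grows instead (0.2 then 0.4), the mean two-stage estimate is 0.36 to 0.38 rather than 0.40. With a constant effect there is no bias.

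**The case against.** The best defense is that the plan names 18 months, not 24. Under linear time that is the midpoint of the two assessments, so full and reduced models aim at the same value when numbers are balanced, and removal does little harm. This stands as far as it goes. But the article does not state linear time, the balance depends on response at 24 months, and with time as a factor the contrast does not exist. The defense therefore limits the size of the problem without justifying the rule.

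Three stronger readings are tempting, and the documents do not support them.
- A reader might infer general inflation of the type I error. With no effect at either time, rejection is only 5.3% to 5.7%. The 7% to 11% arises only for a 24-month claim when there is a 12-month effect. Likewise, with effects 0.4 then 0.2 the rule rejects in 38% to 54% of trials against 32% for a fixed 24-month contrast; this is not a false-positive rate, because a true effect of 0.2 is present.
- A reader might call the pre-test underpowered without qualification. For an interaction of 0.4 its power is 84% to 99.8%; moderate differences are what it misses.
- A reader might say the switch is concealed. The removal rule is stated openly; only its consequence for the contrast is not.

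The fading scenarios are also assumptions. The article plans for 0.4 at both times.

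A separate analysis plan might say more, but the article itself fixes this rule for the confirmatory analysis.

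**Conclusion.** The point holds in conditional form. The elimination rule sits inside the only confirmatory analysis, and the time named for that contrast is not assessed. If an assessed time is intended, the pre-test selects the quantity being tested and the nominal error and coverage for that time are not kept: for a 24-month target, coverage of about 89% to 93% with effects 0.4 then 0.2, and rejection of about 7% to 11% with effects 0.2 then 0. If linear time and the 12/24 midpoint are intended, the shift is nil with balanced numbers and modest otherwise (0.234 against 0.20 in the example). The article does not say which reading applies. All magnitudes rest on the assumed effect patterns, correlations, pre-test level and normal approximation given above.

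**What to change.** In Data Coding and Analysis:
- Delete the sentence that eliminates the interaction.
- Fit time as a factor and always keep group-by-time.
- Replace 18 months by one assessed time, or by the equally weighted average of the 12- and 24-month contrasts from the full model, as the confirmatory contrast. Deleting the rule alone is not enough, since an 18-month contrast cannot be estimated with time as a factor.
- Report the interaction test descriptively.

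This is a change of a sentence or two and needs no new data. If one time is chosen and the effect is truly constant at 0.4, power falls from about 87% to 92% under the present rule to 84% in the normal approximation (about 80% with a t reference on 16 df, the planned level). Choosing the average avoids this loss, but it answers a question about both follow-ups together rather than about the later one.

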**Methods:**

A two-group randomized controlled multicenter trial will examine changes in family-oriented practice and aspects of implementation at baseline as well as at 12- and 24-months follow-up. The CHIMPS-Network consists of 20 clinical centers. The centers in the intervention group receive the support of all of the three implementation interventions: (1) optimal pathways to care, (2) education and a training program for professionals, and (3) systematic screening for children. The centers in the control group do not receive this specific implementation support.

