## Discussion

While research has identified good evidence-based family-oriented interventions like CHIMPS that improve the quality of life of families, little is known about how to implement such interventions most effectively and efficiently in clinical practice in Germany. A strength of this ci-chimps -study is the use of a randomized controlled multicenter trial design with a large and wide-ranging sample. We are including both the child and adolescent as well as adult psychiatric departments and all professionals within a clinical center to get a better understanding of the implementation barriers. It could be a limitation that we can't ensure that the same employees fill out all four measurement times. For the first time in Germany, the translated versions of the questionnaires FFMHPQ and ICQ are used in Germany, so there is no German psychometric data yet. However, both original versions have demonstrated good psychometric validities in previous studies. Thus, it can be assumed that the translated German versions will show good psychometric validities as well.

Generally, it should be considered that ci-chimps is a purely questionnaire-based study, relying on the principle of self-disclosure. Therefore, the tendency toward social desirability cannot be ruled out. However, it can be assumed that this potential trend does not significantly affect the results, because the focus is on the comparison between employees from different clinical centers and the probability is high that this tendency can be found for both groups.

With ci-chimps, the implementation of CHIMPS is being supported for the first time. In previous studies of CHIMPS, there were no specific implementation interventions. Therefore, it should be considered that we can only measure an overall intervention effect. It is not possible to compare the three implementation interventions amongst each other. However, we are sure that with ci-chimps we will be able to identify training needs in clinics in order to improve the implementation of family-oriented interventions like CHIMPS-NET in the future.

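### The sole confirmatory contrast is set at 18 months, when nothing is measured, so it is undefined whenever the group-by-time interaction is kept

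*Protocol article*

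**What the plan says.** In the protocol article, Data Coding and Analysis, the primary endpoint is the change from baseline. It is analysed in a mixed linear model with treatment group, time and baseline value as fixed effects and clinical center as a random effect. The group-by-time interaction is tested and removed if not significant. Then: "The result of the primary analysis is the contrast of the treatment group after 18 months". The next sentence adds: "Only this result will be considered in a confirmatory manner". The two-sided type I error is 5%.

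The schedule differs from this wherever it is given:

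- Abstract, Methods: "at baseline as well as at 12- and 24-months follow-up".
- Study Design: "assessments at baseline as well as at 12- and 24-months follow-up", with calendar dates: "The second assessment will be in May 2022 and the follow-up in May 2023".
- H1, under Aims and Hypotheses, refers to the 12- and 24-month follow-ups.
- Sample Size and Power Calculation: the trial is sized "to detect a difference at 12 and 24 months follow-up".

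No section describes an 18-month assessment. The Discussion, in a remark on staff turnover, mentions that one cannot ensure that "the same employees fill out all four measurement times". That disagrees with three scheduled assessments but defines no further visit.

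**The concern.** The 5% error rate is claimed for one contrast, at a time when no questionnaire is collected. If the plan does not say which estimable quantity stands in for it, the analyst has three candidates: the 12-month contrast, the 24-month contrast, or their average. These can differ if the effect fades or builds after the implementation support ends. A choice made once group results are visible weakens the claim to a confirmatory test. It could also change the trial's conclusion.

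**Working it through.** **1. Does any assessment fall at 18 months?** Study Design ends baseline in May 2021 and defines that as the end of the implementation interventions. From May 2021, May 2022 is 12 months and May 2023 is 24 months. From the earliest baseline month, January 2020, they are 28 and 40 months. Neither count gives a planned 18-month assessment.

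**2. What does the model give at 18 months?**

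- Interaction dropped: one treatment effect common to both follow-ups. The month label has no influence.
- Interaction kept, time as a visit factor: there are contrasts at 12 and 24 months and none at 18.
- Interaction kept, time linear: with two follow-ups the value at (12 + 24)/2 = 18 is the mean of the two contrasts. The article does not say that time is linear.

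**3. The plan's own figure.** Inputs from Sample Size and Power Calculation: d = 0.4, ICC 0.05, 31 per center, 18 centers, two-sided 5%. The variance of a center mean in SD units is V = 0.05 + 0.95/31 = 0.0806. With 9 v 9 centers and a noncentral t on 16 df, power is 80.1%, and 31 is the smallest center size reaching 80%. 18 × 31 = 558, and 558/0.70 = 797.1, rounded up to 798. The stated figures reproduce and involve no 18-month input.

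**4. Power by time point at the actual 8:10 split.** SE of a single-wave contrast = √[0.0806 × (1/8 + 1/10)] = 0.1347.

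- Effect 0.4: noncentrality 0.4/0.1347 = 2.97, power 79.6%.
- Effect 0.2: noncentrality 0.2/0.1347 = 1.48, power 28.7%.
- Average of 0.4 and 0.2 = 0.3, with variance V(1 + ρ)/2, where ρ is the correlation of center means between waves. Power is 68% at ρ = 0.5 and 60% at ρ = 0.8.

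The fade from 0.4 to 0.2 and the range of ρ are assumptions; the article gives neither. A constant center effect with different employees at each wave would imply ρ = 0.05/0.0806 = 0.62, inside that range.

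**5. The same with the plan's interaction rule.** I simulated center means (8 v 10 centers, 31 per wave, t tests on 16 df, 100,000 runs per setting). The interaction was tested at 5%. If significant, the named time point was tested; otherwise the common effect was.

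| ρ | Interaction kept | Reject, 12 months named | Reject, 24 months named | Plain average |
|---|---|---|---|---|
| 0.5 | 29% | 75% | 52% | 68% |
| 0.62 | 36% | 74% | 47% | 64% |
| 0.8 | 59% | 75% | 38% | 60% |

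Allowing for simulation differences, this is about 74-76% for 12 months and 37-52% for 24 months.

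With 0.4 at both waves, naming 12 or 24 months gives 83-89% either way, and the plain average 84-90%.

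**6. Type I error.** Under the null, taking whichever of the three contrasts is significant gives 8-10% false positives (ρ 0.8 to 0.5) if the interaction rule is ignored. If the choice is open only when the interaction is kept, it is about 6%. Part of that excess comes from the pretest itself.

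**The case against.** A reader might infer that the confirmatory test has no data behind it at all. The documents do not support that. Because a non-significant interaction is removed, the plan often ends with a single effect estimated from both follow-ups, and the month then does no work. The test is undefined only in the other branch. That branch matters, though, because it is where the two waves appear to differ.

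A reader might also set 80% power at 12 months against 29% at 24 months as the cost of the ambiguity. Those are the plain single-wave contrasts. The interaction rule pulls both toward the common effect, so the spread is real but smaller.

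Nor is the sample-size wording a separate defect of two contrasts powered as one. It is compatible with a common effect assumed at both follow-ups, and its arithmetic reproduces.

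It can be argued that 18 months was meant as the midpoint, hence the average. That is plausible, but the article neither calls the result an average nor states that time is linear. Equally, nothing in it favours 24 months over 12 months or the average.

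Finally, an employee who completed baseline in November 2020 would reach May 2022 after 18 months. That is an accident of a long baseline window, since the protocol labels that assessment 12 months.

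**Conclusion.** Wrong as written. The one confirmatory contrast names a time that matches no assessment, and it cannot be estimated when the interaction is kept with time as a visit factor. This is a contradiction inside the article, so an analysis plan that is not shown cannot account for it.

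The consequence is moderate. If the effect halves between the waves, the named time point moves the chance of success by roughly 20 to 40 percentage points under the plan's own rule. If the effect is constant, the choice hardly matters. The possible inflation of the 5% error is about one point with the rule applied and three to five points without it. That is what the open choice permits; it does not show that the sponsor would exploit it. The power figures rest on the assumed effect pattern and between-wave correlation, but the contradiction rests on neither.

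**What to change.** In Data Coding and Analysis, replace the 18-month contrast by one that the trial can estimate. This can be a single named assessment, 12 or 24 months, or explicitly the equally weighted average of the 12- and 24-month contrasts. The authors should choose; the documents do not settle it.

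State also that this contrast comes from a model that keeps group-by-time whatever its significance. Changing the month alone would leave a contrast whose meaning depends on a pretest.

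Align H1 and the sample-size text with the chosen contrast, and do so before follow-up data are compared by group. As a side point, reconcile the four measurement times in the Discussion with the three scheduled assessments.

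The cost is a sentence or two and no new data. Always keeping the interaction for a single time point gives up some precision if the effect is constant: about 79-80% power against 83-90% for the pooled effect. Choosing the average avoids that loss.
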